**Physiological measures:**				
• Blood glucose	**●**	**●**	**●**	**●**
• Glycosylated hemoglobin	**●**		**●**	**●**
• Blood pressure	**●**	**●**	**●**	**●**
• Insulin	**●**		**●**	**●**
• Inflammatory markers (hs-CRP, Il-6, TNF-a)	**●**		**●**	**●**
• Serum lipids	**●**	**●**	**●**	**●**
• Body habitus measures (height, weight, and waist circumference)	**●**	**●**	**●**	**●**
				
**Diet, physical activity, medication use, and psychological variables:**				
• 24-hr dietary recall (3 times at each timepoint)	**●**	**●**	**●**	**●**
• 24-hr physical activity recall (3 times at each timepoint except 1 recall only at 3 mths)	**●**	**●**	**●**	**●**
• Medication use	**●**		**●**	**●**
• Depressive symptoms (CES-D)	**●**		**●**	**●**
• Quality of life (SF-36)	**●**		**●**	**●**
• Social desirability	**●**			
				
**Patient Characteristics**				
• Socio-demographic variables	**●**			
• Medical history	**●**			
				
**Process Variables**				
• Retention rate				**●**
• Session attendance				**●**
• Intervention acceptability			**●**	**●**
• Self-efficacy, attitudes, social support, perceived barriers related to dietary changes	**●**	**●**	**●**	**●**

### Randomization

After providing informed consent and completing the baseline assessment, participants are randomized to one of the two diet conditions. Participants are stratified by gender, age (in deciles), and BMI categories (30-34.9, and >= 35-40 kg/m^2^). Within each strata, participants are randomized to the two conditions in randomly permuted blocks of size 3 and 6 using the ralloc program in Stata [49] to ensure that the distributions of gender, age, and BMI are similar between two conditions. The randomization is carried out by the project director who does not interact with participants.

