**Methods and design:**

This is a randomized controlled clinical trial with two equal sized arms. In total, 240 obese adults who meet diagnostic criteria for the metabolic syndrome will be randomized to one of the two conditions: 1) a high fiber diet and 2) the American Heart Association (AHA) diet. In the high fiber diet condition, patients will be given instruction only on achieving daily dietary fiber intake of 30 g or more. In the AHA diet condition, patients will be instructed to make the several dietary changes recommended by the AHA 2006 guidelines. The trial examines participant weight loss and dietary quality as well as changes in components of the metabolic syndrome, inflammatory biomarkers, low-density lipoprotein cholesterol levels, insulin levels, and glycosolated hemoglobin. Potential mediators, i.e., diet adherence and perceived ease of the diet, and the intervention effect on weight change will also be examined.

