### Sample Size Consideration

The required numbers of patients for each arm were based on the primary outcome measure: change in body weight. Sample size was calculated using the method developed by Frison and Pocock [53] and implemented in Stata SE 10 (College Station, Texas, USA). Parameters used in sample size calculations were estimated in our pilot trial and historical data from metabolic patients in our clinics, and we assumed complete randomization of the study subjects to each treatment arms. With 95 complete cases per arm, the hypothesized difference in change in body weight (3.5 lbs) between the arms can be detected with >80% power at 5% significance level.

Considering possible attrition rate of 20%, the number of subjects in each arm should be not less than 120 subjects. Thus, a total of 240 patients will be enrolled in the study.

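### A block of 3 cannot be split equally between two arms, so the stated blocks of 3 and 6 contradict the planned equal arms of 120

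*Protocol article*

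**What the plan says.** The abstract (Methods and design) states: "This is a randomized controlled clinical trial with two equal sized arms".

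Sample Size Consideration plans on the same basis: "With 95 complete cases per arm, the hypothesized difference in change in body weight (3.5 lbs) between the arms can be detected with >80% power". It continues: "Considering possible attrition rate of 20%, the number of subjects in each arm should be not less than 120 subjects". The total is 240.

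The Randomization section gives the allocation rule. "Participants are stratified by gender, age (in deciles), and BMI categories", with two BMI bands, and within each stratum "participants are randomized to the two conditions in randomly permuted blocks of size 3 and 6 using the ralloc program in Stata". The stated purpose is to keep gender, age and BMI similar in the two conditions.

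The article gives no unequal ratio, no third arm and no rule for dividing a block of 3 between two arms.

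**The concern.** Permuted blocks keep two arms equal because each completed block holds the same number from each arm, and that needs an even block size. A block of 3 has no such split. The allocation rule and the planned arm sizes therefore cannot both be right as written.

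The allocation ratio is a basic design fact, and here the reader cannot recover it from the stated rule. If the list follows a fixed 2:1 ratio, one arm ends near 80 rather than 120 and the power claim has to be recalculated. If only the block sizes are misreported, nothing is wrong with the trial itself. Recruitment began in May 2009 and the section describes randomization in the present tense, so a list may already be in use.

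**Working it through.** **Inputs.** From the article: two arms, planned equal; block sizes 3 and 6; 95 complete cases per arm; difference 3.5 lb; power above 80%; 5% level; 20% attrition; 240 enrolled. Assumed: a two-sided test, and an SD of weight change back-solved from the power statement, because the article gives no SD or correlation.

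**The plan's own figure.** 95 / (1 − 0.20) = 118.75, so 119 per arm. The stated 120 is consistent, and 120 × 0.8 = 96 completers per arm.

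**Block arithmetic.** A block of size b splits equally between two arms only if b/2 is a whole number.
- b = 3: 3/2 = 1.5, so no equal split; only 2:1 or 1:2.
- b = 6: 3:3 is possible.
- A fixed ratio common to both sizes with two arms: 2:1 only (2:1 and 4:2). With three arms, 1:1:1 would also fit, but this trial has two.

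**Back-solved SD.** SD = 3.5 / [(1.960 + z_power) × √(2/95)].
- 80% design power: 3.5 / (2.802 × 0.1451) = 8.61 lb
- 85%: 8.05 lb
- 90%: 7.44 lb

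**Power at given arm sizes.** Power = Φ{3.5 / [SD × √(1/n₁ + 1/n₂)] − 1.960}. With SD 8.61:
- 96:96 completers: 3.5 / (8.61 × 0.1443) − 1.960 = 0.856, power 80.4%
- 128:64 completers (160:80 less 20%): 3.5 / (8.61 × 0.1531) − 1.960 = 0.695, power 75.7%

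| Assumed design power | SD (lb) | 96:96 | 128:64 |
|---|---|---|---|
| 80% | 8.61 | 80.4% | 75.7% |
| 85% | 8.05 | 85.4% | 81.1% |
| 90% | 7.44 | 90.3% | 86.7% |

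At 2:1, the design power would need 72 completers in the smaller arm: 3 × 72 = 216 in total, and 216 / 0.8 = 270 enrolled.

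**Arm sizes under each reading.** 4,000 simulated trials of 240 patients, strata equally likely, the two block sizes equally likely. Ranges are central 95% ranges for one arm (the larger one in the first two rows).

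| Reading | 20 strata | 40 strata |
|---|---|---|
| Both sizes at 2:1 | mean 160 (156–164) | mean 160 (154–166) |
| Blocks of 3 at 2:1 in a fixed direction, blocks of 6 at 3:3 | mean 135 (128–141) | mean 136 (128–143) |
| Blocks of 3 in random direction, blocks of 6 at 3:3 | mean 120 (113–127) | mean 120 (112–128) |
| Even blocks of 2 and 4, for comparison | mean 120 (116–124) | mean 120 (115–125) |

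With SD 8.61, an enrolled split of 135:105 (108:84 completers) gives 79.8%. A split of 128:112 (102.4:89.6 completers) gives 3.5 / (8.61 × 0.1447) − 1.960 = 0.850, power 80.2%, against 80.4% at equal arms.

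**Strata.** Ten-year bands over the eligible ages of 21 to 70 give 5 groups: 2 × 5 × 2 = 20 strata, about 12 people each. Ten quantile groups give 2 × 10 × 2 = 40 strata, about 6 people each.

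**The case against.** The strongest reply is that the fault may lie only in the sentence. The article says in two places that the arms are equal or 120 each, and nothing in it suggests 160:80. Sizes 3 and 6 suit a three-arm trial, and the pilot described in the Background had three arms, so carried-over text is a natural explanation. This stands as a possibility. The document cannot settle it, and the sentence needs correcting either way.

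A reader might infer that the trial is running at 2:1 and is underpowered. The article does not support that. It needs a list that nothing in the article describes, and a fall below 80% also needs a design power at or close to 80%, whereas the article says only that power exceeds 80%. At a design power of 85% or 90%, power stays above 80% even at 2:1.

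A second reply is that blocks of 3 could be 2:1 or 1:2 at random. Allocation is then fair on average and the effect on power is about 0.2 points at a 128:112 split. This also stands, but the article states no such rule, and the arms would be slightly less tightly balanced than with even blocks.

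A reader might also infer that age deciles cannot be assigned before enrolment, or that age must be dropped or coarsened as a stratifier. Neither follows. Ten-year bands are a natural reading, quantile cut-points could be set in advance from outside data, and the number of strata is a design preference. Only the ambiguity of the term remains.

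**Conclusion.** The contradiction holds and needs no assumption: a block of 3 has no equal split between two arms, so blocks of 3 and 6 do not deliver the equal arms on which the sample size rests. The defect is in the size 3, not the size 6.

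The consequence ranges from none (a misreported block size), through a negligible change in power (random direction, or about 135:105), to a loss of roughly 4 to 5 percentage points at a fixed 2:1. That last figure is a conditional worst case. It rests on a two-sided test, 20% attrition in both arms and a back-solved SD. It should not be reported as the trial's power.

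The correction is still needed, because the rule is wrong as written and the realised ratio cannot be known from the document.

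**What to change.** 1. Check the allocation list in use for its block sizes and ratio.
2. If the list is 1:1 with even blocks, correct the sentence in the Randomization section to the sizes actually used.
3. If the list contains blocks of 3, generate the remaining allocations at 1:1 with even block sizes (for example 2 and 4, or 4 and 6). If the realised ratio is unequal, restate the arm sizes and the power.
4. State whether age in deciles means ten-year bands (about 20 strata) or ten quantile groups with cut-points set in advance (40 strata).

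The cost is a check of the list and a corrected sentence or, at most, regeneration of the unused allocations and a short amendment. There is no added burden on participants.

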### Intervention

The proposed intervention will consist of 5 sessions during a 3-month intensive phase (1 group session in the 1^st ^month, one individual and one group session during the 2nd month, and biweekly sessions in month 3), and a 9-month maintenance phase of 5 group sessions (during the 4^th^, 5^th^, 7^th^, 9^th^, and 11^th ^months) and one individual session (at the 12^th ^month) for a total of 11 sessions. Individual sessions will be offered at different days and times to accommodate participant schedules.

Patients will have received a diet manual at the first group visit, containing intervention contents by session, home activity worksheets, resources, recipes, and selected menus with nutrition information from restaurants (either AHA or dietary fiber oriented). At the next individual nutrition consultation, an assessment of lifestyle, current dietary habits, challenges to dietary changes and specific nutrition needs, and individualized study goals are reviewed by a registered dietitian. Patients begin tracking their dietary intake in preparation for the third group visit. All group and individualized sessions will be conducted by a registered dietitian initially randomly assigned and trained to the study condition, and will focus on reviewing progress and setting new goals to support achievements. Each session will address any challenges to adherence and facilitate progress toward the patient's new eating style. As self-monitoring can enhance self-control and facilitate problem solving, patients will self-monitor their intake with a food diary, or by using an electronic tracking system. This will facilitate the counting of fiber grams in the high fiber condition, or other food components in the AHA condition. The dietitian will review and return food diaries to assist patients with meeting dietary goals. Dietitian providers are trained in a patient-centered counseling model and strategies from social-cognitive theory to activate patients to take action and responsibility for changing their dietary lifestyle to meet the goal prescribed [50]. All but the first group session will last 1 hour, and will include weighing the patient, a light snack of study appropriate foods, and other tools and methods (The first session lasts 1.5 hours). The first and last individual visits will be 1 hour, and 30 minutes respectively.

Group sessions will target individual food choices, environmental and social influences to dietary intake, lifestyle challenges, and problem-solving techniques in a supportive group format targeting dietary changes over the longer term. Significant others are invited to attend each session and to sign consent to have their weight tracked. Participants unable to attend a session will be offered brief make-up sessions, either by telephone, or in person and are mailed the materials from the missed session.

### High Fiber Diet Condition

Participants randomized to the high fiber condition receive instruction on how to gradually increase their dietary fiber intake to ≥ 30 g fiber per day, with a corresponding increase in non-caloric fluids as necessary to alleviate any gastrointestinal discomfort that may occur because of the increase in dietary fiber [51,52]. The multiple benefits of increasing dietary fiber will be outlined in an engaging, experiential format, with tasting of high fiber foods provided. Participants are encouraged to obtain fiber from a variety of high fiber foods, so they are not relying upon one type of food or fiber (such as high fiber bars or supplements), with a variety of recipes and substitutions suggested allowing for individual tastes, tolerance, and preferences. Participants receive written materials on the fiber content of different foods so they can choose from a vast list of foods that include both soluble and insoluble fiber, such as legumes, barley and other whole grains, nuts, seeds, fruit and vegetables. Self-monitoring will increase awareness and knowledge of intake to attain fiber goals. Participants will be working closely with the dietitian to ameliorate any intestinal discomfort (bloating, gas) associated with increasing fiber intake.

### AHA Diet Condition

Participants randomized to the AHA condition receive step-by-step instruction on the multiple components of dietary change, which includes a diet rich in vegetables and fruits; whole-grains, high-fiber foods; fish, especially oily fish at least twice a week; lean animal and vegetable proteins; learn to distinguish types of fats and oils; minimize intake of beverages and foods with added sugars; choose and prepare foods with little or no salt; and consume moderate to no alcohol intake. A target of 50-55% of calories from carbohydrate, 15-20% from protein, and 30-35% of calories from fat (saturated fat limited to <7% of energy, *trans*-fat to <1% of energy, cholesterol <300 mg/day,) will be suggested. Calorie goals will be calculated and provided to patients by estimating the daily calories needed to maintain the participant's starting weight and subtracting 500-1,000 calories/day (depending on initial body weight and level of activity) to achieve a 1-2 pound per week weight loss (i.e., (starting weight × 12) - 500 kcal). Self-monitoring will increase awareness and knowledge of dietary intake and progress toward AHA goals.

### Physical Activity

We acknowledge the beneficial effect of physical activity on weight loss and most metabolic syndrome components (elevated blood pressure, insulin resistance, and central obesity). However, the present study was designed to assess the effect of a simple dietary recommendation against the AHA diet on weight loss, overall dietary quality and factors of the metabolic syndrome. Therefore, we focus exclusively on dietary modifications during the sessions.

### Safety Precautions

Participants in both arms of the study will be advised to increase fiber slowly, and told to increase fluids to minimize digestive discomfort. Most participants will tolerate an increase in fiber, but some participants may experience gas, bloating, and changes to bowel habits. Participants will be monitored and encouraged to speak about any physiological or psychological difficulties of dietary change to allow the dietitian to assist with transitions to a higher fiber diet or AHA diet, both individually and as part of the group sessions. Over a short period of time (about 1 month or less), most digestive systems will adjust to an increase in dietary fiber. Occasionally, participants are unaware of diverticulosis, and dietary changes may trigger active disease. Participants with active diverticulitis and other gastrointestinal disease are ineligible. Additionally, there may be financial costs associated with making dietary changes, as the participants will be purchasing different foods.

### Training of Intervention Team Providers

All providers will be trained in the intervention delivery models relevant to their randomly assigned condition and will not be trained or have access to training materials for the other condition. Ample opportunities will be provided for developing and practicing the counseling skills to ensure fidelity to the intervention manual.

Four separate 2-hour training sessions are held. The training team includes the PI, a senior dietitian, and a clinical health psychologist. Dietitians will be oriented to the intervention manual for their condition, discuss difficult patient situations, review quality control procedures, and practice counseling skills. The team will work with each dietitian in typical patient interaction simulations. Lastly, each dietitian will present a selected "mock" session as a seminar at UMMS campus for faculty and students.

In order to provide the dietitian with feedback regarding their knowledge of the different interventions, all sessions are digitally recorded, with the senior dietitian listening to each of the first 5 sessions in order to provide feedback, and then 10% of sessions thereafter. Dietitian's knowledge, counseling and teaching skills will meet standards outlined on a certification checklist. Dietitians will attend regular supervision meetings with the senior dietitian, the clinical health psychologist, and PI to discuss study topics, fidelity to protocol, and group concerns.

### Treatment Fidelity

Because both conditions involve dietary interventions that have some subtle but very important differences, contamination and treatment fidelity will be closely monitored. Different dietitian providers are employed for each condition to prevent drift and/or contamination between conditions. During training and supervision, dietitians will be trained to handle situations when patients want to discuss topics not on protocol, with particular emphasis in the increase fiber condition to simply focus on consuming a variety of high fiber foods, without attention to distinction of calories, fats, carbohydrates or protein.

The purpose of fidelity monitoring is two-fold. First, we will ensure that treatment objectives for each condition are met at each session. Second, we will ensure that treatment objectives specific to one condition are not being met in the other condition (i.e., contamination). Two sets of treatment fidelity checklists (one arm-specific provider checklist and one auditor checklist) have been developed. Dietitians will complete the provider checklist after each session. A 10% randomly selected sample of the audio-recorded sessions will be reviewed by the senior dietitian and clinical psychologist. Each will then complete the Auditor Checklist corresponding to that session. When a session is reviewed with less than 85% of treatment-specific objectives met and/or any evidence of contamination (>0% other condition objectives met), the auditor will deliver that information to the PI who will then review the treatment objectives for that session with the counselor and remediate training as needed. This process will be ongoing throughout all treatment waves so that counselor drift can be swiftly corrected.

### Sample Size Consideration

The required numbers of patients for each arm were based on the primary outcome measure: change in body weight. Sample size was calculated using the method developed by Frison and Pocock [53] and implemented in Stata SE 10 (College Station, Texas, USA). Parameters used in sample size calculations were estimated in our pilot trial and historical data from metabolic patients in our clinics, and we assumed complete randomization of the study subjects to each treatment arms. With 95 complete cases per arm, the hypothesized difference in change in body weight (3.5 lbs) between the arms can be detected with >80% power at 5% significance level.

Considering possible attrition rate of 20%, the number of subjects in each arm should be not less than 120 subjects. Thus, a total of 240 patients will be enrolled in the study.

### Statistical Analytic Approach for Primary Aim

The high fiber condition is hypothesized to induce greater weight loss than the AHA condition. We will evaluate the intervention effects on change in body weight using general and generalized linear latent and mixed models (GLLAMM) that have been implemented in Stata SE 10 [54,55]. The commonly used linear mixed models are a subgroup of GLLAMM. In the analysis, each patient is assumed to be independent. First, we will carefully evaluate the covariance structure of the outcome variables across time points, and test whether intervention may induce changes in variability in the outcomes. Proper covariance structure will be identified and prescribed in the final analysis. The participant identifier will be included as random effect, time and group as fixed effect. Treatment effect will be tested using time*group interactions in the models.

The analysis will adjust for potential confounders for weight change, including age, gender, baseline BMI, marital status, education attainment, physician advice regarding weight loss and other nutritional advice exposure prior to and during the trial. We also will evaluate the possible interactions between the intervention indicator and these patient's attributes to assess the presence of differential intervention effects among these subgroups. Session attendance will also be included in the models to determine whether this is a dose-response relationship between number of session attended and the extent of weight loss. Statistical approaches to secondary outcomes are very similar, and thus not discussed in detail.

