### Project Management and Participant Tracking

Under the direct leadership of the project director, project staff will be responsible for: 1) tracking patients to ensure that all necessary data are collected in a timely fashion; 2) assist with developing monitoring reports; 3) providing timely and relevant feedback to the leadership regarding the accuracy of data; and, 4) the day-to-day functioning of the study across all 10 waves of recruitment, intervention and assessment. The tracking system used for monitoring patient activities and providing necessary prompts based on a communication system using Lotus Notes from IBM (Lotus Notes R5.0.11^®^). Multiple levels of password protection are utilized to ensure data security. The tracking system will facilitate timely scheduling of assessments and identification of completed assessments.

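### The primary model assumes independent patients although the diets are delivered largely in groups by arm-specific dietitians, so the 5% test is anti-conservative for any positive within-group correlation

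*Protocol article*

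**What the plan says.** All places are in the protocol article.

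- **Statistical Analytic Approach for Primary Aim:** "In the analysis, each patient is assumed to be independent". The random structure follows: "The participant identifier will be included as random effect, time and group as fixed effect". Here group means the diet arm. The treatment effect is tested by the time-by-group interaction.
- **Intervention:** two group sessions and one individual session fall in months 1 and 2, and month 3 has biweekly sessions of unstated format. Then comes "a 9-month maintenance phase of 5 group sessions" plus one individual session. The total is 11 sessions, which include weighing. The section describes the group format as supportive and aimed at social influences and problem-solving.
- **Treatment Fidelity:** "Different dietitian providers are employed for each condition to prevent drift and/or contamination between conditions". The section also plans for counsellor drift over the treatment waves.
- **Project Management and Participant Tracking:** staff run "the day-to-day functioning of the study across all 10 waves of recruitment, intervention and assessment".
- **Sample Size Consideration:** an individual-level repeated-measures method is used. With 95 completers per arm, a 3.5 lb difference in weight change "can be detected with >80% power at 5% significance level". No ICC or design effect is mentioned.

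**The concern.** Patients are randomised individually, but after randomisation they are treated together. Those who share sessions and a dietitian are likely to have correlated weight changes, and mutual influence is part of what the group format is meant to achieve. A participant random effect handles repeated measures within a person. It does nothing for correlation between people.

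Session groups and dietitians sit wholly within one arm, so their variance does not cancel from the arm comparison. If it is ignored, the primary test rejects too often under the null and the interval is too narrow. A false positive matters here because success is meant to support a simple public health message.

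This is not a detail left to an unseen analysis plan. The article states the assumption and names the random effect.

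**Working it through.** **Inputs from the article:** 240 patients in two equal arms; 10 waves; 95 completers per arm; difference 3.5 lb; 5% significance (taken as two-sided); power above 80%; attrition 20%.

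**Assumed, because the article does not give them:** an ICC for weight change of 0.01 to 0.05, and one or two session groups per arm per wave.

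**The plan's own figures.** The attrition step reproduces: 95/0.80 = 118.75, so 119, against 120 stated. The power cannot be checked, because no SD or correlation over time is given. Power of exactly 80% implies an effective SD of 3.5/[(1.960 + 0.842) × √(2/95)] = 8.61 lb. That is a back-solution, not a confirmation.

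**Group sessions.** 2 + 5 = 7 of 11, or 9 if both month-3 sessions are in groups.

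**Group size.** With one group per arm per wave, 240/10/2 = 12 enrolled and 95/10 = 9.5 completers. With two groups, 9.5/2 = 4.75 completers.

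**Formulas**, with m completers per group:
- Design effect: DE = 1 + (m − 1) × ICC. The true standard error is √DE times the one that the model reports.
- Type I error of the planned test: 2 × [1 − Φ(1.960/√DE)].
- Power of a valid 5% test, starting from exactly 80%: Φ[(1.960 + 0.842)/√DE − 1.960].

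| Groups per arm per wave | ICC | DE | Type I error, planned test | Power, valid test |
|---|---|---|---|---|
| 1 (m = 9.5) | 0.01 | 1.085 | 6.0% | 76.7% |
| 1 | 0.02 | 1.17 | 7.0% | 73.6% |
| 1 | 0.05 | 1.425 | 10.1% | 65.1% |
| 2 (m = 4.75) | 0.01 | 1.0375 | 5.4% | 78.5% |
| 2 | 0.05 | 1.1875 | 7.2% | 72.9% |

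**Degrees of freedom.** One group per arm per wave makes 20 groups, so the arm contrast has about 18 degrees of freedom. With a t reference on 18 df, power is about 75.5% at ICC 0, 72.0% at 0.01, 68.8% at 0.02 and 60.3% at 0.05.

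**Slack in the power claim.** With m = 9.5, keeping 80% by the normal formula needs an unclustered power of about 83% at ICC 0.01, 86% at 0.02 and 92% at 0.05. If the unclustered power were 90%, it would fall to 87.5%, 85.0% and 77.5%.

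**Which random effect is needed.** The time-by-arm contrast rests on within-person change. A group random intercept is constant over time, so it cancels from each person's change and leaves the standard error of that contrast essentially as it was. In a simulated data set with ICC 0.10 in change, the standard error was 1.23 without the group intercept, 1.23 with it, and 1.78 once clustering of change was modelled.

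**The case against.** The strongest case on the other side has four parts.

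1. **Power.** A reader might infer that the stated power is not delivered. The article does not support that. It gives no SD or ICC, and a claim of more than 80% may contain slack. The power figures above start from exactly 80% by assumption, so a fall below 80% is built in. They also describe a cluster-adjusted test, which the article does not plan. The planned test would still reject about 79%, 78% and 76% of the time at ICC 0.01, 0.02 and 0.05, from Φ(0.842/√DE), because its standard error is too small. This objection stands: the main fault in the plan as written is type I error, and the power point must be conditional.

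2. **Group structure.** A reader might infer closed groups, one per arm per wave. The text says neither, and it allows make-up sessions by telephone or in person. This stands as a limit on size: with two groups per arm per wave the inflation is smaller. Clustering through shared sessions and a shared dietitian does not require closed groups.

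3. **Wave and season.** If both arms run in every wave, effects common to both arms cancel from the arm contrast. This stands: only arm-specific group and dietitian variance does harm.

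4. **Dietitian as cluster.** The number of dietitians per arm is not given. With one per arm, dietitian and diet are fully confounded and no model separates them. This stands as a limit on the remedy.

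None of this touches the core. The independence assumption is explicit, the delivery described elsewhere makes it implausible, and neither the model nor the sample size allows for it.

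**Conclusion.** The point holds in a bounded form. For any positive ICC of weight change within session group or dietitian, the primary standard error is too small, the interval too narrow and the 5% test anti-conservative. That direction does not depend on slack in the sample size.

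The size rests on assumptions. For ICC 0.01 to 0.05, type I error is about 6.0% to 10.1% with one group per arm per wave (about 9.5 completers each) and about 5.4% to 7.2% with two. For a valid test, the claim of more than 80% power is unsupported unless the ICC is near zero or the plan has slack. From exactly 80%, with one group per arm per wave, power would be about 77% to 65%, and about 72% to 60% on 18 degrees of freedom.

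It should be corrected before analysis, because it affects the validity of the primary test.

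**What to change.** 1. Delete the sentence that assumes independent patients.
2. Record a session-group identifier and a dietitian identifier for each participant.
3. Model clustering of change: add a session-group-by-time random effect to the repeated-measures model, or a session-group random effect to a model of change scores. Do not rely on a group random intercept alone. The mixed-model framework already chosen can fit this.
4. Base the arm contrast on small-sample, between-group degrees of freedom: about 18 if there are 20 groups.
5. State the number and size of groups and the number of dietitians per arm, and restate power over a stated ICC range.
6. State as a limitation that dietitians are nested in arm. Run a dietitian-level sensitivity analysis only if there are enough dietitians per arm to support it.

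**Cost:** changed wording, two identifiers that should be available from scheduling, slightly wider confidence intervals and a less favourable power figure. From exactly 80%, with one group per arm per wave, restoring 80% by the normal formula would take about 104 to 136 completers per arm (130 to 170 enrolled) at ICC 0.01 to 0.05, against 120 enrolled as planned. The proposal is to accept the lower stated power rather than enrol more patients.
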